# Efficacy and safety of rivaroxaban plus clopidogrel versus aspirin plus clopidogrel in patients with coronary atherosclerotic heart disease and gastrointestinal disease undergoing percutaneous coronary intervention: study protocol for a non-inferiority randomized controlled trial

**DOI:** 10.1186/s13063-023-07236-w

**Published:** 2023-03-21

**Keywords:** Percutaneous coronary intervention, Gastrointestinal disease, Dual antiplatelet therapy, Rivaroxaban, Protocol

## Abstract

**Background:**

Dual antiplatelet therapy (DAPT) with aspirin and a P2Y_12_ inhibitor is recommended for patients with coronary heart disease (CHD) undergoing percutaneous coronary intervention (PCI) to antithrombosis, meanwhile, increasing the risks of gastrointestinal bleeding. Rivaroxaban, a novel oral anticoagulant, combined with a P2Y_12_ receptor inhibitor reduces adverse events in patients with CHD and atrial fibrillation who underwent PCI. The effect of rivaroxaban plus P2Y_12_ inhibitor on reducing bleeding events in patients with CHD and gastrointestinal disease (GID) undergoing PCI remains unclear.

**Method:**

The study is a prospective, single-center, randomized controlled trial. A total of 1020 patients with CHD and GID undergoing PCI will be enrolled. Patients are randomized (1:1) to receive either rivaroxaban 10 mg plus clopidogrel 75 mg daily or aspirin 100 mg plus clopidogrel 75 mg daily; both treatments will last 6 months. The primary endpoint is Bleeding Academic Research Consortium (BARC) type 2–5 bleeding requiring medical intervention. The secondary endpoint is a composite of major adverse cardiovascular and cerebrovascular events (MACCE), including all-cause death, cardiac death, nonfatal myocardial infarction, stent thrombosis, ischemia-driven target vessel revascularization, and stroke.

**Discussion:**

The objective of this study is to evaluate the efficacy and safety of rivaroxaban plus clopidogrel versus aspirin plus clopidogrel in patients with CHD and GID undergoing PCI. We aim to explore an optimized antithrombotic strategy, which achieves the same anti-ischemic effect as standard DAPT without increasing the risk of GIB, for patients with CHD and GID undergoing PCI.

**Trial registration:**

This protocol is registered at the Chinese Clinical Trial Registry under the number ChiCTR2100044319. And this publication is based on version 1.4 of the trial protocol dated Sep 6, 2021.

**Supplementary Information:**

The online version contains supplementary material available at 10.1186/s13063-023-07236-w.

## Introduction

Antithrombotic treatment must be performed in patients with coronary atherosclerotic heart disease (CHD) undergoing percutaneous coronary intervention (PCI). Dual antiplatelet therapy (DAPT) with aspirin and P2Y_12_ inhibitor, which can reduce the risk of ischemic or atherosclerotic thrombotic events (including in-stent thrombosis, recurrent myocardial infarction, and cardiac death) is considerable [1, 2]. Both ischemia and bleeding events significantly influence the outcome of CHD patients [3]. Although DAPT can reduce the risk of thromboembolic events, it is also associated with a higher risk of major bleeding, the most common of which is a gastrointestinal mucosal injury such as ulceration and bleeding [4, 5].

For patients with concomitant *H. pylori* infection, antithrombotic therapy substantially increases the risk of upper gastrointestinal bleeding (UGIB) by 1.8 times (95% CI 1.5–2.1) with aspirin alone and by 7.4 times (95% CI 3.5–15) with DAPT [6]. And UGIB in patients with acute coronary syndrome (ACS) is associated with markedly increased mortality [7]. Previous gastrointestinal diseases (GID) and the combined anti-platelet therapy are the main risk factors for UGIB. Long-term treatment of aspirin inhibits the activity of gastrointestinal cyclooxygenase and results in epithelial to the gastrointestinal mucosa damage in patients with CHD and GID, increasing the risk of bleeding [8]. UGIB can lead to increased mortality and discontinuation of DAPT and failed adequate secondary prevention of CHD subsequently. Out of concern for gastrointestinal damage from DAPT, patients with CHD and GID are less likely to receive revascularization, increasing the risk of cardiovascular death in these patients.

The WOEST trial enrolled patients post-PCI who received oral anticoagulation using a different strategy by antithrombotic regimen, free of aspirin showed a significantly lower incidence of major bleeding among patients assigned to clopidogrel plus a vitamin K antagonist (VKA) (at therapeutic doses) than those assigned to triple antithrombotic therapy with aspirin plus clopidogrel plus VKA (at therapeutic doses) [9]. The PIONEER AF-PCI trial randomly allocated patients to three groups: rivaroxaban 15 mg once daily plus a P2Y_12_ inhibitor for 12 months; rivaroxaban 2.5 mg twice daily plus DAPT for 1, 6, or 12 months; or a dose-adjusted oral VKA plus DAPT for 1, 6, or 12 months. In the two groups receiving rivaroxaban, the rates of clinically significant bleeding were lower, but there were no significant differences between the groups in terms of stroke, myocardial infarction, or death from cardiovascular causes [10]. However, the population in this study was about 94% whites and only about 4% Asians. Previous studies have suggested that the bleeding risk of antithrombotic therapy seems to be higher in the Asian population than that in the white population. The Gemini-ACS-1 study demonstrated that low-dose rivaroxaban did not increase clinically significant bleeding when used with clopidogrel or ticagrelor compared to DAPT. Free of aspirin strategy may be a safe approach for ACS. No risk of thrombotic events due to the discontinuation of aspirin was found [11]. Those studies demonstrated that NOAC (rivaroxaban) as an alternative to aspirin plus a P2Y_12_ inhibitor could achieve similar anti-ischemic effects.

Currently, no clinical studies and guidelines have shown that rivaroxaban can be used instead of aspirin in antithrombotic therapy for patients with CHD and GID. Therefore, we designed a prospective, non-inferiority, randomized controlled trial to assess the efficacy and safety of rivaroxaban plus clopidogrel versus aspirin plus clopidogrel in patients with CHD and GID undergoing PCI.

## Methods

### Study design

The study is a prospective, single-center, non-inferiority, randomized controlled trial. A total of 1020 subjects will be recruited at the Section V of the Cardiology Department of the General Hospital of Northern Theater Command in China. To evaluate the efficacy and safety of rivaroxaban plus clopidogrel versus aspirin plus clopidogrel in patients with CHD and GID undergoing PCI. The study flow diagram is shown in Fig. 1. The SPIRIT Checklist is shown in Supplemental file 1 [12].

**Fig. 1 Fig1:**
[figure not shown]
Flow chart of the study. CHD, coronary atherosclerotic heart disease; GID, gastrointestinal disease; PCI, percutaneous coronary intervention

### Population

Eligible criteria are as follows: Patients 18 to 75 years of age with stable coronary atherosclerotic heart disease or non-ST segment elevation acute coronary syndromes (NSTE-ACS) combined with GID, Global Registry of Acute Coronary Events (GRACE) scores < 140 points, are considered to be enrolled. Patients with GIB or gastrointestinal ulcers that have healed for more than 12 months or the patients who take aspirin accompanied by uncomfortable but tolerable symptoms (e.g., stomachache, abdominal distension) are included. The diagnosis of gastrointestinal disease is determined by the physician based on the patient’s clinical symptoms, the result of the endoscopy, and previous medical history. GID is defined as acute or chronic gastritis, gastric mucosal erosion, GIB or gastrointestinal ulcer healing for 1–12 months, gastrointestinal dysfunction diagnosed by a specialist, or gastrointestinal tumor planning surgery. Patients who met any of the exclusion criteria are excluded. Main exclusion criteria include a GRACE score > 140 points in patients with non-ST segment elevation myocardial infarction (NSTEMI) or ST-segment elevation myocardial infarction (STEMI), severe renal insufficiency (creatinine clearance < 30 mL/min), and previous aspirin or rivaroxaban allergy.

Detailed inclusion and exclusion criteria are listed in Table 1. The subjects met all inclusion criteria and no exclusion criteria are eligible for this study after signing the informed consent form. The informed consent form is provided in Supplemental file 2. To ensure the safety of patients, we will continue to monitor and care for until the end of the study regardless of the reason why participants withdrew from the study. This trial will be terminated in case of any abundance of adverse events or intervention-related complications.

**Table 1 Tab1:** Inclusion and exclusion criteria

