**Inclusion criteria**
• 18 to 75 years of age
• Stable Coronary artery disease or NSTE-ACS with GRACE score < 140 points
• Gastrointestinal diseases
• Taking aspirin with a stomachache, abdominal distension, and other discomforts but can tolerate
• Informed consent

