**Exclusion criteria**
• NSTE-ACS with GRACE score > 140 points or STEMI
• History of intracranial hemorrhage within one month or vital organ bleeding
• Platelet count < 100 × 10^9^/L
• Hemoglobin < 100 g/L
• Active hepatitis or ALT, AST values > 3 × the upper limit of normal
• Severe renal insufficiency (CrCl < 30 mL/min)
• Body weight < 45 kg
• History of aspirin or rivaroxaban allergy
• Not willing to undergo PCI
• Severe progressive disease (e.g., malignant tumor)
• Anticipated life expectancy < 6 months
• Pregnancy, breastfeeding, and childbearing plans
• Long-term use of (N)OAC
• Long-term use of strong CYP3A4 inhibitors or P-glycoprotein inhibitors
• Long-term use of moderately potent CYP2C19 inhibitors or CYP2C19 inducers
• Expected to be unable to tolerate medication for 6 months
• Unable to obtain an informed consent or the researchers think it is not suitable to participate in this trial in any case
• Participating in other ongoing clinical studies

*GRACE* Global Registry of Acute Coronary Events, *NSTE-ACS* non-ST-segment elevation acute coronary syndromes, *STEMI* ST-segment elevation acute myocardial infarction, *ALT* alanine aminotransferase, *AST* aspartate aminotransferase, *CrCl* creatinine clearance (CrCl = [(140-age) × weight (kg) × (0.85 female)]/[0.818 × Scr (mol/L)], *PCI* percutaneous coronary intervention, *NOAC* new oral anticoagulant

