### Interventions

Subjects assigned to the experiment arm should receive rivaroxaban 10 mg plus clopidogrel 75 mg daily. Subjects assigned to the control arm should receive aspirin 100 mg plus clopidogrel 75 mg daily. All subjects are given medication routinely for 6 months. If subjects had never or not routinely taken clopidogrel or aspirin in the pastor taken clopidogrel 75 mg or aspirin 100 mg daily routinely less than five days before inclusion, a loading dose of clopidogrel 300–600 mg or aspirin 300–600 mg should be given within 12 h before coronary angiography.

If GIB occurs during the study, antiplatelet drugs should be discontinued, endoscopic hemostasis under the condition of stable hemodynamics, and Proton Pump Inhibitors (PPI) drug treatment are performed. Three days after hemostasis, subjects are given clopidogrel 75 mg monotherapy daily as soon as possible if the gastric injury is localized or completely hemostatic, no active bleeding relapses, and hemoglobin remains above 90 g/L after blood transfusion. Five days after hemostasis, they return to the original treatment strategy after randomization. But if there is still a small range of active or occult bleeding and the hemoglobin fluctuates above 100 g/L on different days, subjects are given low molecular weight heparin. Seven days after hemostasis, they restore to the original treatment strategy after randomization, and low molecular weight heparin was discontinued at the same time.

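### Eligibility rules conflict for three identifiable patient classes (no aspirin discomfort, bleed or ulcer healed over 12 months, malignant gastrointestinal tumour), so their per-protocol membership cannot be decided

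*Protocol article*

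**What the plan says.** All references are to the protocol article.

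- **Rule for combining criteria (Population).** "The subjects met all inclusion criteria and no exclusion criteria are eligible for this study", once consent is signed. The same paragraph points to Table 1 for the detailed list.
- **Aspirin discomfort.** The Population text admits "Patients with GIB or gastrointestinal ulcers that have healed for more than 12 months or the patients who take aspirin" with uncomfortable but bearable symptoms, so the two descriptions are joined by 'or'. Table 1 has a separate inclusion bullet: "Taking aspirin with a stomachache, abdominal distension, and other discomforts but can tolerate".
- **Healing interval.** The sentence just quoted admits bleeds and ulcers healed for more than 12 months. Two sentences later, the definition of gastrointestinal disease (GID) names "GIB or gastrointestinal ulcer healing for 1–12 months". Table 1 requires "Gastrointestinal diseases" and gives no interval.
- **Tumours.** The GID definition includes "gastrointestinal tumor planning surgery". The Table 1 exclusions name "Severe progressive disease (e.g., malignant tumor" as their example.
- **Loading dose (Interventions).** The provision begins "If subjects had never or not routinely taken clopidogrel or aspirin".
- **Analysis sets (Statistical analysis).** Intention-to-treat (ITT) is everyone randomized. The per-protocol (PP) set is described in a single line as subjects wholly in accordance with the study. The main endpoints are analysed in ITT and repeated in PP as support.

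**The concern.** The trial is defined by its gastrointestinal population and its primary endpoint is bleeding, so the rule on gastrointestinal history decides whom the result describes. The article does not merely leave detail out here. It states rules that give opposite answers when applied literally to the same patient.

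The statistical consequence lies mainly in the PP set. In a non-inferiority trial the PP analysis is a check on the ITT result, and here it is the stated supporting analysis. If the rules cannot tell whether a patient was eligible, someone must decide later. The trial is open-label: investigators know the treatment, and only the event committee and the data analysts are blinded. A late ruling on eligibility could therefore be made with knowledge of arm and outcome. By the Trial status section, 720 of the 1020 patients had been recruited and 506 had completed 6-month follow-up, so most of the decisions concern patients already in the trial.

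**Working it through.** **The plan's own figure.** Inputs from Sample size: 6% in both arms, margin 4.7 points, one-sided 2.5%, power 85%, drop-out 10%.

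n per arm = (1.960 + 1.036)² × 2 × 0.06 × 0.94 / 0.047² = 8.978 × 0.1128 / 0.002209 ≈ 458.5, rounded up to 459. Two arms give 918, and 918 / 0.90 = 1020. The stated total is reproduced. None of these inputs depends on how the eligibility conflict is resolved, unless the resolution changes the event rate, and the article gives no event rate by class of GID.

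**The rules side by side.** Each class is taken as meeting every criterion not in dispute.

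| Patient class | Rule that admits | Rule that does not |
|---|---|---|
| Chronic gastritis with tolerable aspirin discomfort | Population text and Table 1 | none |
| GID, on aspirin without symptoms | Population text, if discomfort is only an alternative | Table 1 discomfort bullet plus the all-criteria rule |
| GID, never on aspirin | Population text, as above; the loading-dose provision points the same way | Table 1 discomfort bullet plus the all-criteria rule |
| Bleed or ulcer healed for more than 12 months, no other GID | Population inclusion sentence | GID definition (1–12 months), which the Population text and Table 1 require |
| Malignant gastrointestinal tumour awaiting surgery | GID definition | Table 1 exclusion example |
| Benign gastrointestinal tumour awaiting surgery | GID definition | none clearly |

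The first row shows that a core population is eligible under every reading. Rows two to five are the disputed classes. The aspirin item matters most, because it decides whether symptom-free or aspirin-naive GID patients belong in the trial at all.

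**Consequence for the analysis sets.** ITT membership needs only randomization, so it is the same under every reading. PP membership requires conformity with the study, and for rows two to five that gives yes under one rule and no under the other.

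**What cannot be computed.** The share of patients in rows two to five is not given. The change in PP size, event rate or power therefore has no basis in the document.

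**The case against.** Several points on the other side are fair.

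- **Healing interval.** The 12-month sentence says that such patients are included. It does not say that healing for more than 12 months is required. It can be read as adding to the definition, so that the two intervals adjoin. Both statements are also in the Population text, and Table 1 states no interval. This stands in part: it reduces the problem to one subgroup, which is still outside the GID definition that the same section makes necessary.
- **Loading dose.** The sentence names clopidogrel or aspirin. A current aspirin user who has never had clopidogrel fits it, so it does not prove that aspirin-naive patients are meant to be enrolled. This stands. The provision sits poorly with a mandatory discomfort criterion, but it is only suggestive.
- **Tumours.** The definition does not say malignant, and a benign tumour awaiting surgery satisfies both passages. This stands, and the conflict is certain for malignant tumours only. A reader might also set planned surgery against the exclusion for expected inability to tolerate 6 months of medication. That criterion concerns tolerance and does not mention interruption for surgery, so the link is inference.
- **Condensed article.** Detailed PP rules may be in the full protocol or analysis plan, and the brevity of the PP line is not the complaint. Condensation explains missing detail, but it does not explain two stated rules that disagree.
- **Bias.** Eligibility is set before randomization, so the ambiguity does not by itself bias the comparison of arms. This stands. The effect is on the PP set and on whom the result applies to.

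**Conclusion.** The contradiction is real and is in the article's own words: one clear conflict (aspirin discomfort as alternative or requirement), one conflict for a subgroup (bleed or ulcer healed for more than 12 months) and one partial overlap (malignant gastrointestinal tumour). For these classes PP membership cannot be decided from the stated rules. It should be fixed before analysis, but it does not undermine the ITT analysis.

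Two stronger readings are tempting. The first is that the study population is undefined and all 1020 patients are affected. The documents do not support this: ITT is defined, and a patient with gastritis and tolerable aspirin discomfort passes the gastrointestinal and aspirin criteria on every reading. The second is that case mix moves the 6% event rate and so erodes power or makes the 4.7-point margin more generous in relative terms. Differences in bleeding risk between the classes are plausible, but the article links no event rate to any reading of the criteria, so any such figure would rest on a chosen rate and not on this defect.

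The conclusion assumes that the article reproduces version 1.4 of the protocol faithfully. If version 1.4 is consistent, the error is in the article, and the correction is to the publication.

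**What to change.** 1. Reconcile the Population text, both parts of Table 1 and the loading-dose provision in Interventions with one another and with protocol version 1.4. The result should be one statement on whether aspirin discomfort is required or alternative, one on the healing interval, and one on tumours awaiting surgery. Which rule applies is for the clinical leads to decide.
2. Before the database is analysed, have staff who are blind to arm and outcome classify all enrolled patients under the single rule, and use that classification to form the PP set. The investigators who treat the patients know the allocation and should not make these rulings.

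The cost is a short amendment and an eligibility re-check. Table 2 schedules previous history, admitting diagnosis and drug therapy at enrollment, so the re-check should be possible from data already collected. This assumes that healing dates and aspirin symptoms were recorded there or can be found in the medical records. Sample size, margin and the ITT analysis need no change on this account.

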**Inclusion criteria**
• 18 to 75 years of age
• Stable Coronary artery disease or NSTE-ACS with GRACE score < 140 points
• Gastrointestinal diseases
• Taking aspirin with a stomachache, abdominal distension, and other discomforts but can tolerate
• Informed consent
**Exclusion criteria**
• NSTE-ACS with GRACE score > 140 points or STEMI
• History of intracranial hemorrhage within one month or vital organ bleeding
• Platelet count < 100 × 10^9^/L
• Hemoglobin < 100 g/L
• Active hepatitis or ALT, AST values > 3 × the upper limit of normal
• Severe renal insufficiency (CrCl < 30 mL/min)
• Body weight < 45 kg
• History of aspirin or rivaroxaban allergy
• Not willing to undergo PCI
• Severe progressive disease (e.g., malignant tumor)
• Anticipated life expectancy < 6 months
• Pregnancy, breastfeeding, and childbearing plans
• Long-term use of (N)OAC
• Long-term use of strong CYP3A4 inhibitors or P-glycoprotein inhibitors
• Long-term use of moderately potent CYP2C19 inhibitors or CYP2C19 inducers
• Expected to be unable to tolerate medication for 6 months
• Unable to obtain an informed consent or the researchers think it is not suitable to participate in this trial in any case
• Participating in other ongoing clinical studies

*GRACE* Global Registry of Acute Coronary Events, *NSTE-ACS* non-ST-segment elevation acute coronary syndromes, *STEMI* ST-segment elevation acute myocardial infarction, *ALT* alanine aminotransferase, *AST* aspartate aminotransferase, *CrCl* creatinine clearance (CrCl = [(140-age) × weight (kg) × (0.85 female)]/[0.818 × Scr (mol/L)], *PCI* percutaneous coronary intervention, *NOAC* new oral anticoagulant

### Recruitment

Advertisement through posters and an outpatient publicity board is used to identify potential participants to reach the required sample size.

### Randomization and blind

Before randomization, all enrolled subjects are assessed for randomization. Subjects with any of the following conditions shall not be randomized: withdrawal of informed consent, voluntarily withdrawal from the trial, the investigator determining that random antithrombotic regimens cannot be accepted, and unwilling or unable to undergo PCI.

After the assessment, the subjects are getting a random number. Based on the number, subjects are randomized (1:1) to the experiment arm (rivaroxaban plus clopidogrel) or the control arm (aspirin plus clopidogrel) by the block randomization table. Two investigators enroll subjects. The random number was generated by an independent professional statistician using the SPSS 25.0 software. According to the order generates a random number and informs the number to the authorized doctor who obtains informed consent and decides the intervention. This trial is an open-label design. The investigators and the subjects know which drugs the subjects are using, but the independent event assessment committee and data analysts do not know which drugs the subjects are using.

